### Adverse event reporting and harms {22}

Adverse events will be inquired for during each clinical visit and monitored using the LiSERS questionnaires when commencing the intervention. All adverse events reported spontaneously after the study medication has been provided (i.e., after baseline) by the patient or observed by the investigator or staff will be recorded. Due to an average delay of diagnosis of 1 year in Europe and an average life expectancy of 3 years for patients with ALS, a considerable proportion of the included ALS patients are expected to decease during the 2-year follow-up. These deaths are of natural disease progression and will not be reported as SAEs. All AEs will be followed until they have abated or until a stable situation has been reached. Depending on the event, follow up may require additional tests or medical procedures as indicated, and/or referral to the general physician or a medical specialist.

Expedited reporting of suspected unexpected serious adverse reactions (SUSARs) of immediate concern to patient safety will be done by the sponsor through the web portal EudraVigilance to the IRB; this suffices as notification to the competent authority. The remaining SUSARs will be recorded in an overview list accompanied by a brief report highlighting the main points of concern that will be submitted once every half year to the IRB.

The Sponsor will report expedited all SUSARs to the competent authorities in other member states, according to the requirements of the member states. The expedited reporting will occur not later than 15 days after the sponsor has first knowledge of the adverse reactions.

For fatal or life-threatening cases, the term will be maximal 7 days for a preliminary report with another 8 days for completion of the report. In addition to the expedited reporting of SUSARs, the sponsor will submit, once a year throughout the clinical trial, a safety report to the accredited IRB and competent authorities of the concerned member states.

This safety report consists of: a list of all suspected (unexpected or expected) serious adverse reactions, along with an aggregated summary table of all reported serious adverse reactions, ordered by organ system, per study, and a report concerning the safety of the patients, consisting of a complete safety analysis and an evaluation of the balance between the efficacy and the harmfulness of the medicine under investigation.

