### Outcomes {12}

#### Primary outcomes

The primary endpoint of this study is a composite endpoint, defined as time to death from any cause or respiratory insufficiency (tracheostomy or the use of non-invasive ventilation for ≥22 h per day for ≥10 consecutive days).

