#### Secondary outcomes

Combined effect on daily functioning and overall survival based on a joint model of survival and ALSFRS-R total scores.Daily functioning, defined as mean change from baseline in ALSFRS-R total score. Disease progression will be monitored using the ALSFRS-R, which is a validated 12-item questionnaire designed to evaluate the functioning of respiratory, bulbar, fine and gross motor function in ALS patients [22]. The total score ranges from 48 (no limitation in daily activities) to 0 (total inability). The ALSFRS-R slope, the difference in scores standardized for time, is often used as measure of disease progression in clinical trials and is significantly associated with survival [23].Respiratory function, defined as mean change from baseline in Slow Vital Capacity (SVC). The SVC is associated with survival in ALS patients [24]. The obtained estimates of the vital capacity will be recorded in liters and standardized using the GLI-2012 reference standard [25].Change in outcome of Plasma creatinine. Plasma creatinine is a part of the safety tests and will be used as one of the secondary endpoints to monitor disease progression [26]. Plasma creatinine is well correlated with functional decline, muscle strength and is highly predictive for overall survival. Due to the effect of disease progression on plasma creatinine, Cystatin C will be used for monitoring kidney function as safety parameter [27].Clinical disease stage, defined as mean time spent in each stage of the King’s and ALS Milano-Torino staging systems. The King’s staging system is a simple clinical staging system, which defines four stages of ALS. The first three stages are defined by functional involvement of a region: bulbar, upper limbs and lower limbs. The number of regions involved gives the stage. Stage 4 is reached if swallowing (4A) or respiratory (4B) difficulty is severe enough to require intervention. This procedure takes the form of a semi-structured interview. MITOS is a similar clinical staging system, in which the stages are defined as loss of independence on the four domains of the ALSFRS-R: swallowing, walking/self-care, communicating and breathing [28]. Studies have shown that both King’s staging and the ALS-MITOS correlate with survival [29, 30].Safety based on the safety assessments including neurological examinations, clinical laboratory evaluations, vital signs and frequency of adverse events (AEs) or serious adverse events (SAEs). (S)AEs will be categorized according to the Common Terminology Criteria for Adverse Events and will be rated for severity and association with study drug.Tolerability defined as time-to-discontinuation of assigned treatment since randomization.Change from baseline in urinary P75^ECD^. P75 is a neutrotrophin receptor that is expressed after motor neural damage and excreted through the urine [31]. Hence, presence of P75^ECD^ in the urine is indicative for the degeneration of motor neurons. P75^ECD^ has been shown to increase over time in patients with ALS and correlates well with measures of functional decline. Moreover, the marker is associated as independent predictor of survival. Therefore, P75^ECD^ may have the utility as a potential pharmacodynamic biomarker and slowing of a rising urine level may be indicative of a biological effect.Change from baseline in plasma Neurofilament light and heavy chain. Neurofilament light and heavy chains in ALS are well known to be correlated with prognosis and remain relatively stable over time [32]. A change in the expression of neurofilament light and/or heavy chain may, therefore, be considered as supporting evidence of disease amelioration in ALS.Neuropsychological status, defined as change from baseline on the ECAS and ALS-FTD-Q. Approximately 35% of the patients, with ALS, experience cognitive or behavioral impairment. The cognitive and behavioral impairment may increase as disease progresses [33]. The neuropsychological status of patients will be evaluated using the Edinburgh Cognitive and Behavioral ALS Screen (ECAS) [34]. The ECAS is independent of motor disability and evaluates five cognitive domains: language functions, executive functions, and letter fluency, memory and visuospatial functioning. If available, ECAS version A and B will be alternated to prevent a training effect in patients. The questionnaire has a behavior screen with a carer interview, this part will not be performed in this study. In addition, we will evaluate behavioral disturbances using the ALS frontotemporal dementia questionnaire (ALS-FTD-Q) [35]. The ALS-FTD-Q is a validated instrument for the screening of behavioral disturbances in ALS. The ALS-FTD-Q has 25 items (including three cognitive items: memory, concentration, and orientation in time), with a 4-point rating scale; the maximum score is 100. A higher score indicates more behavioral disturbances.Global quality of life (QoL), defined as change from baseline on the visual analog scale (single-item scale) and EQ-5D. QoL will be measured using a visual analog scale (single-item scale): a horizontal line of 100 mm ranging from 0 (worst imaginable QoL) to 100 (perfect QoL) [36]. Generic QoL will be measured using the EQ-5D. The EQ-5D measures the health status in terms of five dimensions: mobility, self-care, usual activities, pain and depression. From the EQ-5D a quality-adjust life year (QALY) can be calculated, which is required for cost-utility analysis if a drug is beneficial for patients with ALS [37]. If a patient deceases during the follow-up period, the date will be recorded. If a patient reaches the criteria for respiratory insufficiency (tracheostomy or the use of non-invasive ventilation for ≥22 h per day for ≥10 consecutive days), the date this criterion was met will be recorded and the patient will no longer be part of the study. The time point for all secondary outcomes is month 24.

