### Composition of the data monitoring committee, its role and reporting structure {21a}

A DSMB has been established to provide oversight of safety and efficacy considerations during the conduct of the current study and to provide advice to the sponsor regarding actions the committee deems necessary for the continued protection of patient enrolled in the study. The DSMB is an independent multidisciplinary group that, collectively, has experience in the management of patients with ALS, and in the conduct and monitoring of randomized clinical trials. DSMB members are independent of the sponsor and all investigational study sites.

The DSMB will provide recommendations about stopping or continuing the trial. To contribute to enhancing the integrity of the trial, the DSMB may also formulate recommendations relating to the selection, recruitment, and retention of patients, their management, improving adherence to protocol-specified regimens and retention of patients, and the procedures for data management and quality control. The DSMB may decide to prematurely terminate the trial for safety when the interim safety analysis indicates that serious adverse effects occur significantly more often in one group than in the other group, or when there is evidence for accelerated disease progression in the treatment arm compared to the placebo arm. Additionally, the DSMB may decide to prematurely terminate the trial for efficacy when any of the stopping rules as described previously are met.

The advice(s) of the DSMB will only be sent to the sponsor of the study. Should the sponsor decide not to fully implement the advice of the DSMB, the Sponsor will send the advice to the reviewing IRB, including a note to substantiate why (part of) the advice of the DSMB will not be followed.

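### Deaths expected during follow-up are attributed to ALS in advance and exempted from SAE reporting, with no condition on the cause of the individual death

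*Protocol article*

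**What the plan says.** The Protocol article, Adverse event reporting and harms {22}, argues from diagnostic delay and life expectancy in ALS that "a considerable proportion of the included ALS patients are expected to decease during the 2-year follow-up". It then says: "These deaths are of natural disease progression and will not be reported as SAEs". No clause limits this to deaths whose cause has been assessed, and none makes an exception for a suspected drug reaction.

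Four other places bear on it:

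- The same section sets expedited reporting of SUSARs, including: "For fatal or life-threatening cases, the term will be maximal 7 days for a preliminary report".
- Under Secondary outcomes, the safety outcome uses AEs and SAEs, which "will be rated for severity and association with study drug".
- The section on the data monitoring committee {21a} lets the DSMB end the trial for safety on either of two grounds. The first applies "when the interim safety analysis indicates that serious adverse effects occur significantly more often in one group than in the other group". The second ground, an alternative to it, is worded: "or when there is evidence for accelerated disease progression in the treatment arm compared to the placebo arm".
- The primary endpoint is "defined as time to death from any cause or respiratory insufficiency", and Table 1 collects survival data at screening, baseline and each quarterly visit.

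**The concern.** Exempting the expected fatal course of a disease from SAE reporting can be legitimate, particularly when death is part of the primary endpoint. The difficulty is that the sentence settles the cause for a whole class of deaths before any of them has occurred. Nothing in its wording separates a death from ALS from a death in which lithium may have played a part.

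The distinction matters in this trial. The Discussion names the side-effects of lithium as the main risk and reports one earlier lithium trial in ALS that stopped partly because of many SAEs. It adds that the later placebo-controlled trials raised no major safety concerns. The protocol also has dedicated procedures for lithium intoxication. A fatal reaction is therefore something the plan should be able to recognise in the individual case, and at this point the text steers sites away from doing so.

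**Working it through.** No figure in the protocol depends on the exemption, so the main check is to follow one death through the text. Two small calculations then show what is and is not at stake.

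**1. A possibly drug-related death under the literal rule**

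| Step in the plan | Requires | Result if the death is exempt |
|---|---|---|
| SAE reporting {22} | Death reported as an SAE | Not reported |
| Safety outcome (Secondary outcomes) | An AE or SAE to rate for association | The death itself is not rated |
| Fatal SUSAR, 7 days plus 8 {22} | A serious event suspected to be a reaction | No stated way in |
| Annual safety report {22} | A list of suspected serious reactions | Same gap |
| DSMB, first safety ground {21a} | Serious adverse effects by arm | Not counted |
| DSMB, second safety ground {21a} | Evidence of accelerated progression | Can contribute, without a cause |
| Primary endpoint | Death from any cause | Counted, without a cause |

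The SUSAR sentence presupposes that some deaths are examined as possible drug reactions. The exemption does not say which.

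**2. Would counting the deaths change the SAE comparison?**

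The arm sizes, 114 and 57, come from Trial design {8}. Assumption, for illustration only: k drug-related deaths on lithium, none on placebo, and no other SAEs. Two-sided Fisher exact test:

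| k of 114 v 0 of 57 | p if counted | If exempt |
|---|---|---|
| 3 | 0.55 | 0 v 0 |
| 5 | 0.17 | 0 v 0 |
| 8 | 0.053 | 0 v 0 |
| 10 | 0.032 | 0 v 0 |

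Two to four per cent of 114 is 2.3 to 4.6 patients. At that level the between-arm test would not be significant with or without the exemption.

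**3. Would the primary endpoint reveal such deaths?**

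Assume the planning hazard ratio of 0.50. With 2:1 allocation the lithium share of events is roughly (2 × 0.50)/(2 × 0.50 + 1) = 1/2, so about 20.5 of the 41 interim events fall in each arm. Adding k lithium deaths gives a crude ratio of [(20.5 + k)/2]/20.5:

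- k = 3: 23.5/41 = 0.57
- k = 5: 25.5/41 = 0.62

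The futility bound in Table 2, Z = 0.36, corresponds at 41 events to a hazard ratio of exp(−0.36/√(41 × 2/9)) = exp(−0.119) = 0.89. Both crude ratios lie well below it. If lithium works as assumed, a few fatal reactions would leave the endpoint looking favourable. This is a rough approximation: the added deaths also raise the event total slightly above 41.

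**The case against.** The strongest reply is that the sentence has a narrower meaning. It follows a statement about deaths expected from the natural history of ALS, so a death suspected to be due to lithium is arguably outside it. The fatal-SUSAR timeline in the same section has a use only on that reading. This may well be the intention, but the text does not state it. It declares the cause rather than making the exemption depend on one.

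The reply is also right on several limits:

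- The exemption concerns reporting the death as an SAE. A serious event before it, such as intoxication or renal failure, is a separate event that is still to be recorded and rated.
- A reader might infer that deaths are hidden from the DSMB. The documents do not support that: death from any cause is in the primary endpoint, survival is collected at scheduled visits, and accelerated progression is a stopping ground in its own right.
- A reader might infer that deaths are compared by arm only at 41 events and at the end. Those are the efficacy and futility looks. The DSMB section mentions a separate interim safety analysis and gives no schedule for it.
- A reader might infer that tens of deaths leave the SAE data. The 72 planned events combine death with respiratory insufficiency and the split is not given, so no count can be derived.
- SAE definitions and cause-of-death forms may be in the full protocol, which is not shown. Their absence from the article is not the point. The point is an affirmative rule that the article does state.

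**Conclusion.** The point holds as a defect in a stated rule. As written, the exemption is unconditional on cause. Followed literally, it takes a possibly drug-related death out of SAE reporting, out of the rating for association with study drug and out of the first DSMB safety ground. It is also in tension with the fatal-SUSAR sentence.

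Its size should not be overstated. Deaths still reach the efficacy data and can reach the DSMB through the accelerated-progression ground. In the illustrative range of two to five drug-related deaths, the between-arm test would not be significant either way. What is lost is case-by-case causality review and SUSAR capture. The all-cause endpoint does not replace these, because it carries no cause and, under the assumed benefit, would still look favourable with a few such deaths added.

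The conclusion rests on the literal wording. If the sponsor meant only deaths judged to be from ALS, the correction is one of wording. The illustrative rates and the equal split of interim events are assumptions, not figures from the protocol.

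**What to change.** Reword the sentence in Adverse event reporting and harms {22} so that:

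- the exemption covers only deaths that the blinded investigator has individually recorded as due to ALS progression;
- every other death is reported as an SAE with a relatedness assessment;
- the fatal-SUSAR sentence is reconciled with this, so that the way into that route is explicit.

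In the section on the data monitoring committee {21a}, state that the DSMB receives a separate table of all deaths by arm, with date and recorded cause. Keep this table apart from the SAE comparison. Merging ALS deaths into that comparison would contradict the exemption, largely repeat the all-cause endpoint and dilute a small drug-related signal.

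The cost is one cause-of-death assessment per death and one table per DSMB safety review. The design, sample size and primary analysis do not change.

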### Frequency and plans for auditing trial conduct {23}

The sponsor (or its authorized representative) has the obligation to follow this study closely to ensure that the study is conducted in accordance with the protocol, International Conference on Harmonisation (ICH) and GCP guidelines, national and international regulatory requirements, and the current Declaration of Helsinki throughout its duration, by means of personal visits to the investigator’s facilities and other communication. These visits will be conducted to evaluate the progress of the study, verify that the rights and well-being of the patients are protected, and verify the reported clinical study data are accurate, complete, and verifiable from source documents. This includes review of Informed Consent Forms, results of tests performed as a requirement for participation in this study, and any other medical records (e.g., laboratory reports, clinic notes, IP dispensing log, pharmacy records, patient-completed questionnaires, telephone logs, ECGs) required to confirm information contained in the eCRFs. The monitoring frequency during the study should be at least 2 visits per year per center, of which at least 1 on-site visit. Staff should be available during these visits for discussion on the conduct of the study as well as to facilitate the review of the clinical study records and resolve/document any discrepancies found during the visit. All monitoring activities will be reported and archived. In addition, monitoring visits will be documented at the clinical site by signature and date on the study-specific monitoring log.

### Plans for communicating important protocol amendments to relevant parties (e.g., trial patients, ethical committees) {25}

Amendments are changes made to the research after a favorable opinion by the accredited IRB has been given. All substantial amendments will be notified to the IRB, as they requires IRB approval, and to the competent authority. A “substantial amendment” is defined as an amendment to the terms of the IRB application, or to the protocol or any other supporting documentation, that is likely to affect to a significant degree:The safety or physical or mental integrity of the patients of the trial;The scientific value of the trial;The conduct or management of the trial;The quality or safety of any intervention used in the trial; andThe addition of a new experimental compound.

Non-substantial amendments will not be notified to the accredited IRB and the competent authority, but will be recorded and filed by the sponsor. Examples of non-substantial amendments are typing errors and administrative changes like changes in names, telephone numbers and other contact details of involved persons mentioned in the submitted study documentation.

### Dissemination plans {31a}

Results from the study will be submitted for publication by the investigators only, in international peer-reviewed medical journals.

## Discussion

In this study we aim to provide conclusive evidence about the life-prolonging potential of lithium carbonate in a genetic ALS subgroup. As such, we have defined the primary endpoint as a composite of respiratory free survival, which has been recommended by the FDA and EMA for clinical trials in ALS [50, 51]. Even though a minority of ALS patients will be eligible for participation in the current trial due to need of homozygosity for the C-allele at SNP rs12608932 in *UNC13A*, there are several aspects of the trial that will hopefully ensure prompt enrolment. The TRICALS infrastructure allows access to a large population of potential trial participants, as each site sees between 37 and 264 new ALS patients yearly, based on a feasibility questionnaire [7]. We expect that 75 to 80% of these patients would be eligible for genetic screening due to the use of the TRICALS risk-profile score described previously, which allows for more patients to enroll than when using conventional eligibility criteria [18]. Finally, the event-driven and group-sequential design overcomes potential limitations encountered in previous trials, and minimizes the exposure of patients to ineffective treatment arms [54].

The main risk associated with this study is the side-effects of lithium. As multiple trials with lithium carbonate have been performed in ALS, the side-effects of lithium carbonate in the target population of this study are well known, as well as pitfalls pertaining to its use [14, 15, 20]. One previous trial was discontinued due to extensive patient discontinuation rates, partially due to the high number of SAEs [20]. While the following placebo controlled trials reported no major safety concerns [14, 15], we aim to minimize the risk of lithium intoxication by excluding patients at increased risk, and by frequent monitoring of both the plasma lithium concentration as well as earlier detection of looming intolerability through the LiSERS questionnaire.

Recent advancements in the field of ALS therapeutics could possibly affect the conduct of this study, as new treatment options are either in development or in the process of market authorization. A combination of oral sodium phenylbutyrate and ursodoxicoltaurine has been found to delay the rate of progression in a 6-month study and has been approved recently by the Canadian health authorities [55]. Furthermore, positive results of genetic therapy, Tofersen, specifically aimed at mutations in *SOD1* have been published [56]. Both of these compounds are yet to be approved by the relevant authorities in countries where the current study takes place. Nevertheless, should registration follow, an amendment to the current protocol will be made to include sodium phenylbutyrate-ursodoxicoltaurine, and Tofersen as a concomitant therapies, where new patients are preferably on a stable dose 30 days prior to randomization.

Genetic testing is part of the study protocol and can be a challenging topic to discuss with patients [57]. As blinding to UNC13A status is impossible in the current study, results will be shared with patients. This leads to some considerations regarding genetic and prognostic counseling. The life-time risk for developing ALS is 1:350 for people from European descent; homozygosity for the C-allele at SNP rs12608932 adds an almost negligible increase from to 1.13 in 350 [58]. Furthermore, the C-allele at SNP rs12608932 is a common genetic polymorphism; approximately 14% of the total population are homozygous [58, 59]. It is, therefore, a risk factor for ALS, but does not cause ALS or confer the disease in a Mendelian manner. As such, there is no need to refer patients homozygous for the C-allele at SNP rs12608932 to a clinical geneticist for additional counseling or testing of family members.

Homozygosity for the C-allele at SNP rs12608932, however, does have a large effect on the disease phenotype. The median survival for patients homozygous for the C-allele in *UNC13A* is shorter by approximately six months, though UNC13A homozygous patients may still present with a slow disease course and long survival [60, 61]. In the ENCALS survival model, homozygosity for the C-allele at SNP rs12608932 was not an independent predictor of survival [19]. This is due to the fact that homozygosity for the C-allele at SNP rs12608932 is associated with clinical characteristics that have a larger survival effect such as a bulbar onset and a delayed age at onset [19, 61]. As such, the *UNC13A* genetic status does not add predictive information on top of what can be said based on clinical characteristics alone. It is part of standard clinical care to discuss prognosis with patients based on their clinical characteristics. This is of particular importance for those patients where the disease progression rate will likely be rapid as it directly affects clinical decisions such as weight management and respiratory support.

